### 3.5.2 Sample size calculation

The sample size estimation, which is carried out using hypothesis testing two population means (Aday & Cornelius, 2006). The data is taken from a previous study conducted by Chen et al. (2011). The baseline score was; mean=32.32 with standard deviation (SD) 6.76, post intervention score has increased to 36.22 with SD 6.95. The hypothesis of no difference is to be tested at the 5% ( $\alpha$ ) 0.05 level of significance and power ( $1-\beta$ ) = 0.80 (80%) (2-tailed). The hypothesis testing two population means sample size estimation as follow:

$$H_0 : \mu_1 = \mu_2$$

$$H_1 : \mu_1 \neq \mu_2$$

$$n = \frac{2\sigma^2 [Z_{1-\alpha/2} + Z_{1-\beta}]^2}{(\mu_1 - \mu_2)^2}$$

$\mu_1$  = estimated mean (larger)

$\mu_2$  = estimated mean (smaller)

$$n = \frac{2(6.76)^2 [1.96 + 0.842]^2}{(36.22 - 32.32)^2}$$

$$n = \frac{(91.40) (7.85)}{15.21}$$

$$n = 47$$

The above sample size formula is valid only for the simple random or systematic random sampling method. This study will employ a cluster sampling design, so it requires a larger sample size to achieve the same precision and power (Aday & Cornelius, (2006).

Therefore, the calculated sample size using the above formula need to be multiplied by the design effect (DEFF). According Aday & Cornelius, (2006), the DEFF =  $1 + (b - 1) roh$ , where  $b$  = cluster size and  $roh$  = rate of homogeneity (intracluster correlation). Assuming a cluster size of 6 and intracluster correlation of 0.05 (Davies et al., 2008), so the DEFF is 1.25. This means that such cluster sampling requires double the sample size of above,  $n = 47 \times 1.25 = 59$  of respondents is needed for each group.

Hence, a total of 71 are considered adequate to recruit for a dropout rate and potential of attrition (20%). Thus, total 142 eligible criteria of the respondents is needed to be approached in order to retain 118 respondents (59 respondents per group) at the end of the study.

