Referring to the control group, there were two studies that received usual care for their control group (Borges & Ostwald, 2008; Waxman et al., 2003). The control group in Lincoln's study received the same leaflet regarding foot care as intervention group but not any teaching instruction (Lincoln et al., 2008). However, Baba's study did mention that group A received written education while group B received an interactive educator-led session (Baba et al., 2014). One study divided the sample into two groups (Low risk and high risk) but both group had received same education program (Calle-Pascual et al., 2002). In Nadia's study, nothing was not mentioned about any care received by the control group (Nadia et al., 2012). Eight studies only involved one group pre-test and post-test (Fujiwara et al., 2011; Aikens et al., 2015; Chen et al., 2011; Williams et al., 2014; Tang et al., 2012; Ko et al., 2011; Deakin et al., 2006; Dettori et al., 2005).

Time of follow-up and evaluation were varied across the studies. Seven studies were measured at the baseline (Time 1) and evaluation (Time 2) (Baba et al., 2014; Fujiwara et al., 2011; Waxman et al., 2003; Borges & Ostwald, 2008; Chen et al., 2011; Ko et al., 2011; Dettori et al., 2005). Another six studies were measured at baseline (Time 1), follow-up (Time 2) and evaluation (Time 3) (Aikens et al., 2015; Lincoln et al., 2008; Calle-Pascual et al., 2002; Williams et al., 2014; Tang et al., 2012; Deakin et al., 2006). One study was measured at baseline (Time 1), immediately after the program (Time 2), follow-up (Time 3), and evaluation (Time 4) (Nadia et al., 2012).

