Outcome measured in these articles were included foot self-care (e.g. inspection, hygiene, appropriate socks and shoe, nail care, professional treatment), self-efficacy, empowerment, problem solving, knowledge, acculturation, medication adherence, social support, emotional, anxiety and depression, quality of life, diabetes health care utilization, satisfaction with care. The secondary outcome included clinical findings or signs and symptoms of foot problems (e.g. assessed for peripheral neurologic assessment, vibration perception threshold, pain and disability, morbidity, ulcer, lesion, amputation, tinea pedis and callus). Other significant outcomes in relation with diabetes also were measured such as Self-Monitoring Blood Glucose (SMBG), Fasting Blood Sugar (FBS), Glycoslated haemoglobin (HbA1c), lipid profile, blood pressure, Body Mass Index (BMI), waist circumference, retinal examination and urinalysis.

The instruments used varied across these studies. Most of the researcher used a questionnaire as their research tool. The self-reported questionnaire may have validity issues, less precise and misclassification. Different instrument used to measure the same outcome may influence the outcome. For example, there were studies which measured the adherence of diabetes foot self-care with "Nottingham Assessment of Functional Footcare (NAFF)" by Lincoln et al., (2007) (Lincoln et al., 2008; Baba et al., 2014). While in other studies the similar tool was developed by the researchers itself (Chen et al., 2011; Nadia et al., 2012). Another example was for the clinical findings for incidence of foot problems. Chen's study used the Michigan Neuropathy Screening Instrument developed by Moghtaderi et al. (2006) (Chen et al., 2011). However, in another study, the foot problems were identified from the subject's medical records (Lincoln et al., 2008). It would be happened as different settings have different research protocols and practice guidelines.

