| Chen et al., (2011)

Quasi-experimental

Taiwan         | Effectiveness of a health promotion programme for farmers and fishermen with type-2 diabetes in Taiwan

Theory: not mentioned | To examine the diabetes control and foot self-care capability in farmers and fishermen following introduction of a multi-stage, multi-disciplinary team and community-based small group health promotion programme

N=323                                                                                                                                                             | Approach: group, one-to-one, health setting and home

Content:
1) personal health assessment (foot ulcer, clinically significant neuropathy and vasculopathy, and poor diabetic control) and community-based small group health promotion education (diet control, medication compliance, foot care, physical activity); followed by 2) individually tailored home phone counselling was given 1–3 times per person for about 15–30 minutes

Delivered by diabetes educators and public health nurses, metabolic physicians and plastic surgeons. | Baseline - 6 months

Outcome:
Peripheral neurological assessment.
Peripheral vascular assessment
Foot self-care capability

HbA1c, BMI, Waist circumference (WC), | PO: Foot self-care behaviour improved significantly after the program ( $p < 0.01$ )

SO:
The neuropathy Screening Index and right side ankle brachial pressure index improved significantly ( $p < 0.01$ )                                 | The health promotion programme benefits to many physiological indicators; peripheral neuronal and vascular functions | Good                    |

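### Section 3.5.2 uses the 3.90-point before-after change of a one-group study as a between-arm difference, so the 80% power holds for 0.58 SD and not for 3.90 points on the DFSBS

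*Combined protocol and SAP*

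**What the plan says.** Section 3.5.2 (Sample size calculation) bases the sample size on a 2011 health promotion study: "The baseline score was; mean=32.32 with standard deviation (SD) 6.76, post intervention score has increased to 36.22 with SD 6.95". The larger and smaller means become the two population means in the two-sample formula, with SD 6.76, two-sided 5% significance and 80% power. The result is 47 per arm, 59 after a design effect of 1.25, 71 after an allowance for dropout, and 142 in total.

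Other sections describe the source study:
- Section 2.3.6 includes it in the list attached to "Eight studies only involved one group pre-test and post-test".
- Section 2.3.6 cites it, on how adherence to foot self-care was measured, for "While in other studies the similar tool was developed by the researchers itself".
- Table 2.2 gives N = 323 and measurement at baseline and 6 months, describes no control group, and reports a within-group result: "Foot self-care behaviour improved significantly after the program".

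This trial has two arms. Foot self-care behaviour is the primary outcome (section 2.6). It is measured with the 16-item DFSBS (section 3.6.1), and Table 3.5 compares intervention with control by mixed ANOVA over T1, T2 and T3. No section gives a DFSBS SD, an expected control-arm change, a target difference between arms, or a reason why the before-after figures should carry over.

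**The concern.** A before-after change contains everything that moves scores over time: the programme, repeated questioning, attention and general drift. A difference between arms contains only what the programme adds to usual care. The two are equal only if the control arm stays still.

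The protocol gives some reason to expect movement. In Table 2.2, the usual-care group of the three-arm trial improved (p < 0.05). In Table 3.4, controls are visited and complete the full questionnaire set at weeks 4 and 12, and at week 12 they are reminded to maintain their health care.

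There is also a question of scale. A difference of 3.90 points on another tool has no fixed meaning on the DFSBS, and the DFSBS scoring is itself unsettled. Section 3.6.1 ends with a 1-to-5 rating per item (16 to 80 if summed), while the Part C form in the appendix prints 0 to 7 per item (0 to 112 if summed).

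At stake is how a null result can be read. As written, nobody can say which difference in DFSBS points the trial was able to detect.

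**Working it through.** **Inputs from section 3.5.2.** Means 32.32 and 36.22; SD 6.76; two-sided alpha 0.05 (z = 1.96); power 0.80 (z = 0.842); design effect 1 + (6 − 1) × 0.05 = 1.25; 59 completers per arm. The design effect and the 59 are used as stated.

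**1. The plan's figure reproduces.**
- Difference: 36.22 − 32.32 = 3.90.
- n = 2 × 6.76² × (1.96 + 0.842)² / 3.90² = 47.18. The plan uses 47; rounding up gives 48.
- 47 × 1.25 = 58.75, so 59. Then 59 × 1.2 = 70.8, so 71, and 2 × 71 = 142.
- Power check: SE = 6.76 × √(2 × 1.25/59) = 6.76 × 0.2058 = 1.39; 3.90/1.39 − 1.96 = 0.84; Φ(0.84) = 80%.

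**2. What that power refers to.** The formula depends only on the ratio 3.90/6.76 = 0.577. The calculation therefore supports 80% power for an arm difference of 0.58 SD on whatever scale is used.

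**3. Type of SD.** 6.76 is the spread between people at baseline, which is what a two-sample formula needs. Using the post-intervention SD of 6.95 gives 50 per arm before clustering, and the pooled SD gives 49, so this choice hardly matters.

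**4. Control-arm improvement (assumed sizes).** Power = Φ(difference/1.39 − 1.96), comparing post-intervention scores only:

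| Control gain, share of 3.90 | Arm difference | In SD units | Power |
|---|---|---|---|
| 0 | 3.90 | 0.58 | 80% |
| 10% | 3.51 | 0.52 | 71% |
| 25% | 2.93 | 0.43 | 56% |
| 50% | 1.95 | 0.29 | 29% |

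**5. Effect of using baseline.** For a comparison of changes, the SD becomes 6.76 × √(2(1 − r)), where r is the correlation between baseline and follow-up. The design effect is held at 1.25.
- r = 0.5: the SD stays 6.76 and the table is unchanged.
- r = 0.7: the SD is 6.76 × 0.775 = 5.24 and SE = 5.24 × 0.2058 = 1.08. Power is 77% at 2.93 and 44% at 1.95.
- r below 0.5: power is lower than in the table.

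**6. Different scale (assumed SDs).** With the difference fixed at 3.90, a DFSBS SD of 5 gives 97%, 8 gives 66% and 10 gives 47%. These show only that the direction is open. On a scale with wider spread, the difference in points could grow as well, and at a constant 0.58 SD power would stay at 80%.

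**The case against.** The strongest reply is that borrowing a standardised effect from a related study is ordinary practice. Only the ratio 0.58 enters the formula, so a change of questionnaire matters only if the standardised effect differs. That stands as far as it goes, but section 3.5.2 does not say it is borrowing a standardised effect, and it makes no allowance for change in the controls.

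Several other objections stand:
- The three-arm trial's control improvement is reported only as p < 0.05, without a size, and the same row reports a significant difference between groups. The 10%, 25% and 50% gains are therefore illustrations.
- The planned analysis uses repeated measurements, so the post-only figures are not this trial's power. The only DFSBS stability figure, a two-week retest coefficient of 0.92 in Table 3.2, is an optimistic guide to the correlation over 4 to 12 weeks.
- This programme is specific to foot care and has weekly follow-up, while the source programme was broader. The true effect could exceed 0.58 SD.
- Section 3.5.2 does not name the score behind 32.32 and 36.22. That it comes from the researcher-made foot self-care tool is inferred from section 2.3.6 and Table 2.2.

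A reader might also infer that 6.76 is the SD of a change, or that the sample-size arithmetic is wrong. Neither is so: the text labels 6.76 as the baseline SD, and the figures reproduce.

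**Conclusion.** The concern holds as an unsupported planning assumption. The stated power is valid for a standardised arm difference of 0.58 SD, given 59 completers per arm and a design effect of 1.25. It is power for 3.90 points on the trial's outcome only if controls do not change and the DFSBS has an SD of 6.76, and the documents support neither condition.

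A reader might conclude that the trial is underpowered. The documents do not show that, because the net effect, the DFSBS SD and the correlation over time are all unknown. Under the assumed control gains, post-only power runs from 71% down to 29%. A correlation above 0.5 would raise those figures for a change comparison and one below 0.5 would reduce them. Whether the cluster size of 6 is right is a separate matter and plays no part in these figures.

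**What to change.** Keep the sample size and reword section 3.5.2:
- State that 59 completers per arm give 80% power for a between-arm difference of 0.58 SD at a design effect of 1.25, and do not describe this as 3.90 DFSBS points. Say that the 3.90 is a before-after change in one group.
- Add the power for smaller differences: about 56% at 0.43 SD and 29% at 0.29 SD, post-only.
- Settle one DFSBS scoring, then convert to points as 0.577 × SD, using the pilot SD with its 95% confidence interval.
- Use a T1-T2 correlation only if the pilot really takes repeat measurements. Section 3.6.2.2 describes none; only the budget line for three visits suggests it.

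The cost is rewording and a calculation from a pilot that is already planned, with no added participants. There are two drawbacks. The stated figure becomes less favourable, and the conversion to points will be imprecise. Section 3.7.1 sets the pilot at 10% of the required sample, about 14 people, for which the 95% limits of an SD are roughly 0.72 to 1.61 times the estimate (normality assumed). With the 50 pilot respondents in the budget they are about 0.84 to 1.25 times.

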### 3.4 Population

#### 3.4.1 Targeted population

There are approximately 1631 of residents staying in Peninsular RSK (Table 3.1). Currently the RSK Seremban was closed due to renovation. Majority of them are independent and able to perform their activity daily living (e.g. bathing, eating, grooming, etc.) independently. The targeted population in this study is, the respondents (elderly with diabetes) must be diagnosed with diabetes. The number of elderly diagnosed with diabetes who are totally independent in each RSK is about 40-50 residents.

Table 3.1 Number of RSK Inmates by Institution and Sex, 2013  
source: Jabatan Kebajikan Masyarakat, Malaysia

| Institution          | Male       | Female     |
|----------------------|------------|------------|
| RSK Bedong           | 193        | 99         |
| RSK Cheng            | 103        | 84         |
| RSK Cheras           | 97         | 78         |
| RSK Pengkalan Chepa  | 73         | 62         |
| RSK Johor Bahru      | 176        | 102        |
| RSK Kangar           | 72         | 74         |
| RSK Seremban         | 0          | 0          |
| RSK Taiping          | 94         | 79         |
| RSK Tanjung Rambutan | 164        | 81         |
| Total         | 972 | 659 |

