### 3.5 Sample

#### 3.5.1 Sampling method

A probability cluster sampling with specific eligibility criteria will be used in this study. There are nine RSK in the Peninsular Malaysia. However, for the time being, RSK Negeri Sembilan was closed due to renovation process, so there are total eight of RSK in Peninsular Malaysia. RSK Cheras will be excluded for pilot testing and RSK Pengkalan Chepa located in West Peninsular Malaysia. Hence, six RSK will be allocated randomly using random sequence number generator where each group (RSK) is having equal chance to be neither in the intervention group nor control group. Here, there are three RSK will be taken in intervention group and another three RSK will be placed under control group. Figure 3.2 showed how the sample will be selected and grouped in this study.

[figure not shown]

Figure 3.2 Sampling selection process

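### The design effect uses a cluster size of 6, which cannot fit 59 completers per group in three homes; at the plan's own ICC of 0.05 a cluster-respecting comparison has about 62% power (41% on 4 df), not 80%

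*Combined protocol and SAP*

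**What the plan says.** Section 3.5.2 sizes the trial as a comparison of two means, with two-sided 5% significance and 80% power. The inputs come from an earlier study: a baseline "mean=32.32 with standard deviation (SD) 6.76", after which the "post intervention score has increased to 36.22 with SD 6.95". The difference is 3.90 and the SD used is 6.76, giving 47 per group. The section then says this figure is valid only for simple or systematic random sampling. It multiplies by a design effect, DEFF = 1 + (b − 1) × roh, where b is defined as the cluster size: "Assuming a cluster size of 6 and intracluster correlation of 0.05", so DEFF = 1.25 and 59 per group are needed. The same sentence says that "such cluster sampling requires double the sample size of above". Recruitment is set at 71 per group (142 in total) so that 59 per group (118) remain.

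Section 3.5.1 sets the unit of allocation: six homes are randomised, and "there are three RSK will be taken in intervention group and another three RSK will be placed under control group". Section 3.4.1 adds that "The number of elderly diagnosed with diabetes who are totally independent in each RSK is about 40-50 residents".

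Section 3.9 and Table 3.5 plan a mixed between-within ANOVA and a repeated-measures ANOVA on individual respondents. Neither mentions a term for home.

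**The concern.** The value entered for b does not describe the trial. Three homes of six residents make 18 per group, not 59. The number 6 does match the number of homes randomised, but the section does not say where it came from. The error does not depend on its origin, because 6 is not the cluster size of this design.

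The design effect is the only allowance for clustering in the sample-size justification. If it is too small, the stated 80% is not a property of the design. What that costs depends on the analysis. An analysis that respects the homes has less power than claimed. One that ignores them rejects too often when the program has no effect.

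The text also conflicts with itself: it says clustering doubles the requirement while multiplying by 1.25.

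**Working it through.** **Inputs.** From section 3.5.2: difference 36.22 − 32.32 = 3.90, SD 6.76, two-sided 5%, 80% power, ICC 0.05, 59 completers and 71 recruited per group. From section 3.5.1: three homes per arm. From section 3.4.1: 40–50 eligible residents per home.

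**1. The plan's own figure.**
- n = 2 × 6.76² × (1.96 + 0.842)² / 3.90² = 47.2, so 47.
- DEFF = 1 + (6 − 1) × 0.05 = 1.25, and 47 × 1.25 = 58.75, so 59.
- Power at 59 per group with DEFF 1.25 is 80.0%. The arithmetic reproduces; the input b is what fails.

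**2. Cluster size implied by the design.**
- Completers: 59/3 = 19.67 per home. DEFF = 1 + 18.67 × 0.05 = 1.93.
- As recruited: 71/3 = 23.67 per home. DEFF = 1 + 22.67 × 0.05 = 2.13.

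**3. Power at 59 per group.**
- SE = 6.76 × √(2 × 1.933/59) = 1.731, and 3.90/1.731 = 2.25.
- Normal formula: Φ(2.254 − 1.96) = 61.5%.
- Six homes in two arms leave 4 df (critical value 2.776). Noncentral t power is 40.6%.
- If all 71 per group completed, the normal formula gives 65%.

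**4. Difference detectable with 80% power at 59 per group.**
- Normal: 2.802 × 1.731 = 4.85 points.
- 4 df: the multiplier that gives 80% power is 3.76, and 3.76 × 1.731 = 6.5 points.

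**5. Sensitivity to the ICC** (59 per group; values other than 0.05 are assumptions).

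| ICC | Power, normal | Power, 4 df |
|---|---|---|
| 0.01 | 82% | 59% |
| 0.02 | 76% | 53% |
| 0.05 (plan) | 62% | 41% |
| 0.10 | 46% | 30% |

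**6. More residents in the same six homes** (ICC 0.05). With three homes per arm, b rises with n, so the requirement solves n = n0 × [1 + (n/3 − 1) × 0.05]. With the unrounded n0 of 47.16 this gives n = 47.16 × 0.95/(1 − 47.16 × 0.05/3) = about 209 per group, or about 70 per home.

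| Residents per home | DEFF | Power, normal | Power, 4 df |
|---|---|---|---|
| 40 (120 per group) | 2.95 | 74% | 51% |
| 50 (150 per group) | 3.45 | 77% | 53% |

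As residents per home grow without limit, the SE tends to 6.76 × √(2 × 0.05/3) = 1.234, and 4-df power tends to about 66%.

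**7. The analysis with no term for home.**
- Such a test uses SE = 6.76 × √(2/59) = 1.245, while the true SE is 1.731.
- With no true effect it rejects when the observed difference exceeds 1.96 × 1.245 = 2.44 points, which is 2.44/1.731 = 1.41 true standard errors. The two-sided probability is about 16%.
- With a true difference of 3.90 it rejects with probability of about 80%, but that is not power at the 5% level.

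**The case against.** **The ICC is uncertain.** This stands as a condition. At an assumed ICC of 0.01 the normal formula gives 82%, so a reader who took 62% as the upper limit of the true power would go beyond the documents. But the plan chose 0.05, and its 80% should hold at that value. Even at 0.01 the 4-df figure is 59%.

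**Repeated measures may recover precision.** They may. If baseline adjustment with an assumed correlation of 0.6 reduced both variance components by the factor 1 − 0.36 = 0.64, the SE would be 0.8 × 1.731 = 1.385. Power would then be about 80% (normal) or 57% (4 df). The plan gives no within-person correlation, and its formula takes no credit for one, so this does not support the 80% as derived.

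**A null result would be misread as failure of the program.** A reader might infer this as the main consequence. It follows only if the analysis accounts for home. The ANOVA described in section 3.9 does not say that it will, and without such a term the main hazard is a false positive.

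**47 × 1.93 = 91 per group would restore 80%.** A reader might infer this too. It holds b at 19.7, which needs more homes. In three homes, 91 per group means 30.3 per home, DEFF 2.47 and about 70% power on the normal formula.

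**Adding residents is pointless with three homes per arm.** That is too strong. Normal-formula power rises from 62% to 74–77% at 40–50 per home. Section 3.7.2 invites all independent residents, and Appendix 6 budgets questionnaires for 250 respondents in the main study. What stands is that 80% is not reached.

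**Conclusion.** The cluster size in section 3.5.2 is wrong as written, because it is incompatible with 59 completers per group in three homes. That 6 was taken from the number of homes is a reasonable inference, but the text does not state it.

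At the plan's ICC, SD and difference, the design effect is 1.93 rather than 1.25, and the power at 59 per group is about 62% (normal) or 41% (4 df) rather than 80%. These figures assume an unadjusted comparison of two means, equal-sized homes, an analysis that accounts for home and a true two-sided 5% level. They move materially with the ICC. Within the 40–50 eligible residents per home, the present six homes do not reach 80% by either calculation at ICC 0.05. The 16% type I error applies if the ANOVA is run without a term for home at the same ICC.

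This must be corrected, because it is the only justification given for the sample size.

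**What to change.** In section 3.5.2:
- Replace b = 6 with the expected completers per home: 19.7 (DEFF 1.93), or 20 if rounded (DEFF 1.95). Quote the DEFF that belongs to the b chosen.
- Delete 1.25 and the statement that the sample size must double.
- Restate what 59 per group in three homes per arm provides: about 62% power (normal) or about 41% (4 df) for 3.90 points, or a detectable difference of about 4.85 or 6.5 points.
- State that these figures assume an ICC of 0.05 and an analysis that accounts for home, and show the range over other ICCs.

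The cost is a rewritten paragraph and a less favourable stated power. No extra participants are required.

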## Abstract

**Background:** Diabetes related foot problems can affect health status. Foot self-care behaviour is an essential management in preventing foot complications of diabetes. Self-efficacy theory has been reported to improve foot self-care behaviour of elderly with diabetes.

**Objective:** Main aim here is to develop, implement and evaluate the effects of self-efficacy enhancing program on foot self-care behaviour of elderly with diabetes in Rumah Seri Kenangan, Peninsular Malaysia.

**Methods:** Randomised Control Trial Design, single blind with two groups; intervention and control will be used as a study design. The study will be conducted in Rumah Seri Kenangan, Peninsular Malaysia. A probability cluster sampling will be chosen and a total of 142 respondents who met the inclusion criteria will be invited for participation. During education program, the intervention group will be given a seminar and demonstration about foot self-care behaviour. Meanwhile the control group will receive a usual health care. A series of follow up will be continued for 12 weeks. Pre and post questionnaires which includes demographic data and clinical characteristics, foot self-care behaviour, foot care efficacy expectation, foot care outcome expectation, knowledge on foot care and quality of life will be distributed within a given time frame. The data will address each of the research questions by descriptive and inferential statistics.

**Conclusion:** The aim of the education program will that, after completed the program, the foot self-care behaviour, foot care efficacy expectation, foot care outcome expectation, knowledge on foot care and quality of life will be improved with respect to the program delivered. Future expectation, the Self-efficacy theory can be incorporated in diabetes education to enhance foot self-care behaviour and improve physical and psychosocial outcome of elderly with diabetes.

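### At the plan's own 20% attrition, 142 residents leave about 113 to 114, not the stated 118, because 59 per group was multiplied by 1.2 instead of divided by 0.8

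*Combined protocol and SAP*

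**What the plan says.** Section 3.5.2 (Sample size calculation) computes 47 per group from a two-mean formula, multiplies by a design effect of 1.25, and arrives at 59 per group. It then makes the allowance for loss: "Hence, a total of 71 are considered adequate to recruit for a dropout rate and potential of attrition (20"%). The 71 is a per-group figure, since the next sentence doubles it: "Thus, total 142 eligible criteria of the respondents is needed to be approached in order to retain 118 respondents (59 respondents per group"). No formula is shown for the step from 59 to 71.

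The Abstract (Methods) repeats the total in other terms: "a total of 142 respondents who met the inclusion criteria will be invited for participation". Section 3.7.2 (Step 2) says something different about invitations: all independent elderly residents of the homes are to be invited.

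**The concern.** Section 3.5.2 makes three statements about the same people: 142 are recruited, 20% are lost, and 118 remain. They cannot all be true. A dropout rate is a fraction of those who enter, so the number to recruit is the evaluable number divided by one minus the rate. Multiplying by one plus the rate gives too few.

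The evaluable sample behind the 80% power statement is therefore not reached if the loss is as large as the plan assumes. Anyone who later compares actual recruitment and retention with 142 and 118 would be using two targets that do not match the stated rate.

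**Working it through.** **Inputs**, all from section 3.5.2 unless noted:
- Two-sided alpha 0.05, power 80%.
- "The baseline score was; mean=32.32 with standard deviation (SD) 6.76"; "post intervention score has increased to 36.22 with SD 6.95". The difference is 36.22 − 32.32 = 3.90. The plan uses SD 6.76.
- Cluster size 6 and intracluster correlation 0.05, as the plan takes them.
- Attrition 20%.
- Equal allocation (section 3.5.1): "there are three RSK will be taken in intervention group and another three RSK will be placed under control group".

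**Reproducing the plan's figures**
- n per group = 2 × 6.76² × (1.96 + 0.842)² / 3.90² = 47.18, which the plan rounds to 47.
- Design effect = 1 + (6 − 1) × 0.05 = 1.25.
- 47 × 1.25 = 58.75, rounded to 59.
- 59 × 1.2 = 70.8, rounded to 71; 2 × 71 = 142. This matches the plan exactly.
- The usual form does not match: 59 / (1 − 0.20) = 73.75, rounded to 74; 2 × 74 = 148.

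So 142 reproduces only as the evaluable number multiplied by 1.2.

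**What 142 retains**
- At 20% loss: 142 × 0.80 = 113.6 in total, 71 × 0.80 = 56.8 per group. In whole residents this is 113 or 114, which is 4 to 5 short of 118.
- Loss at which 118 remain: (142 − 118) / 142 = 24 / 142 = 16.9%.
- Check on the usual form: 148 × 0.80 = 118.4, which does retain 118.

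**Power on the plan's own inputs** (normal approximation, effective n = n / 1.25)

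Power = Φ( 3.90 / (6.76 × √(2 / effective n)) − 1.96 )

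| Evaluable per group | Effective n | Power |
|---|---|---|
| 59 | 47.2 | 80.0% |
| 56.8 | 45.44 | 78.5% |

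The difference is about 1.5 percentage points.

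**How 142 is described**

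| Place | Term used |
|---|---|
| Section 3.5.2, sentence giving 71 per group | to recruit |
| Section 3.5.2, sentence giving 142 | approached |
| Abstract, Methods | invited |
| Section 3.7.2, Step 2 | all independent residents are invited; no number given |

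**The case against.** The best defence is that the effect is slight and that the 20% may have been meant as a loose margin on 59. The first part stands: six residents and 1.5 points of power are small. Another choice in the same formula matters about as much. With the post-intervention SD of 6.95, the number before the design effect rises from 47.2 to about 49.9 per group. The second part is weak, because the text ties the 20% to dropout and attrition and names the number to be retained.

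Three stronger readings might be inferred, and the documents do not support them.

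- **That 142 cannot retain 118.** It can, if loss is 16.9% or less. The shortfall is conditional on the assumed 20% occurring.
- **That refusals shrink the sample further.** Section 1.7 does expect some refusals, and section 3.5.2 and the Abstract use words that suggest 142 is an invitation count. But section 3.7.2 invites all independent residents, section 3.4.1 puts independent residents with diabetes at about 40 to 50 per home (240 to 300 over six homes, before the other criteria), and Appendix 6 prices honoraria and main-study questionnaires for 250 respondents. Invitations are not clearly capped at 142, so no extra loss can be claimed. What remains is inconsistent wording.
- **That a target of 148 would restore 80% power.** That holds only if 59 per group stands. The 59 uses a cluster size of 6, whereas three homes per arm means 59 / 3 = 19.7 residents per home. At the plan's intracluster correlation of 0.05, the design effect would be 1 + 18.7 × 0.05 = 1.93. This is a separate and larger matter.

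**Conclusion.** The retained figure in section 3.5.2 is wrong as written. At the plan's own 20% attrition, 142 residents leave about 113 to 114 (56.8 per group), and power is about 78.5% instead of 80%. The 118 is reached only if loss is 16.9% or less. The effect is small but the arithmetic is not in doubt: it rests only on figures in section 3.5.2. The power value also takes the plan's difference, SD and design effect of 1.25 as given, and says nothing about whether that design effect is right. The differing terms for the 142 call for reconciliation and do not add to the shortfall.

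**What to change.** In section 3.5.2, make one of two restatements:
- with 20% attrition, 142 enrolled leaves about 113, with about 78.5% power on the plan's inputs; or
- 142 enrolled retains 118 provided attrition does not exceed 16.9%.

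In any revised calculation, settle the design effect first, then divide the resulting evaluable number per group by 0.8. No fixed new target should be set before that; 148 applies only if 59 per group is kept.

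In section 3.5.2 and the Abstract, describe the target as the number enrolled, and bring this into line with section 3.7.2, which invites all independent residents.

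The restatement costs one or two sentences, a slightly less favourable figure, and no additional residents. Recruiting more would be a separate decision that follows from the revised design effect.
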